## Abstract

**Supplementary Information:**

The online version contains supplementary material available at 10.1007/s00270-023-03477-z.

## Introduction

Knee osteoarthritis (OA) is a leading cause of chronic disability and economic burden [1]. Many patients with knee OA are resistant to conservative treatment options (analgesia, physiotherapy, and steroid injections) and may not yet be suitable for surgery. A growing body of evidence supports genicular artery embolisation (GAE) as a potential treatment option for this cohort of patients. GAE is a novel procedure in which abnormal vasculature arising from branches of the genicular arteries is embolised [2–9]. There are established feasibility and safety using permanent microspheres in patients with mild to moderate knee OA [6, 7]. Early results indicate that GAE may reduce both synovitis and OA symptoms [6]. Despite the growing body of evidence, generalisability is limited by small sample size, short follow-up, and lack of control groups to enable assessment of the placebo effect [10]. Furthermore, previous data have identified subsets of patients who do not report clinical benefit following GAE, despite an apparently technically successful procedure [6]. Emerging pain literature has explored whether specific neural and/or behavioural factors predispose to the central facilitation of pain and may therefore be able to predict treatment response following GAE [11].

The rationale of the current study is to improve data generalisability on the effectiveness of GAE, whilst testing the hypothesis that GAE is more effective than a sham procedure in treating mild to moderate knee OA.

## Materials and Methods

Genesis II is a double-blind randomised sham-controlled superiority trial that will test the hypothesis that GAE is more effective than a sham procedure. The study will also assess participant neuropsychological factors in an attempt to better understand how chronic pain affects treatment response to GAE. Contrast-enhanced MRI of the affected knee will be performed to assess imaging markers of success. Safety, cost-effectiveness, analgesia use, and patient reported outcome measures (PROMS) will all be investigated as part of this study. The study has full ethical approval (IRAS study number: 286849), and there is no objection to clinical investigation from the UK Medicines and Healthcare products Regulatory Authority (MHRA) (Ref: CI/2022/0016/GB).

The study team has extensive experience of GAE, having completed the GENESIS study [6]. Patients will be recruited from orthopaedic surgery, rheumatology, general practice, physiotherapy, or self-referral. Participants must fulfil all inclusion criteria and none of the exclusion criteria (Table 1). Provided that they meet the eligibility criteria, patients with prior GAE may participate in the trial for the opposite knee. Participant consent form is provided in Online Appendix A.

**Table 1 Tab1:** Inclusion/exclusion criteria

Inclusion criteria	Exclusion criteria
Participant is willing and able to give informed consent for participation in the study	Rheumatoid arthritis
Age ≥ 45 years	Infectious arthritis
Grade 1–3 knee OA on X-ray as per Kellgren–Lawrence Grading Scale	Severe (Grade 4) knee OA on Kellgren–Lawrence scale
Knee pain for ≥ 3 months that is resistant to conservative non-surgical treatment (e.g. physiotherapy, steroid injections, weight-loss programs, platelet-rich plasma injections)	Renal impairment (eGFR < 45, from medical records or blood test)
Able to lie flat for ≥ 6 h, assessed by asking how participants sleep (bed, chair recumbent, semi-recumbent) and what prevents them from lying flat overnight (breathlessness, back pain, etc.)	Bleeding diathesis (INR > 1.6, platelets < 50,000) or other bleeding risk, such as warfarin that cannot be stopped easily (e.g. patients with metallic heart valves) assessed by asking the patient and from medical records
Baseline VAS (visual analogue scale, 0–100) ≥ 50	Requires oxygen on ambulation
	Life expectancy < 1 year
	Communication difficulty due to language barriers
	Contraindication to magnetic resonance imaging (MRI)
	Known allergies to barium sulphate, 3-aminopropyltrialkoxysilane, polyphosphazene or IV radiopaque contrast agent
	History of peripheral arterial disease with intermittent claudication and/or rest pain
	Pregnancy or positive pregnancy test (due to fluoroscopy radiation exposure)
	Any other significant disease or disorder which, in the opinion of the recruiting physician, may put the participants at risk because of participation in the study, or may influence the result of the study or the participant’s ability to participate

### Interventions

#### GAE/Sham Procedure

Participants will be randomly allocated (1:1) to GAE or sham treatment using a computational generator created using code in Excel. The generator is maintained on a password protected research server. On the procedure day, an unblinded trained radiographer will inform the staff performing the study procedure of the participant’s allocation. At the 1-month and 6-month visits, participants will be asked which group they believed they were allocated to in order to assess accuracy of blinding. At 6 months post-randomisation, the participants and the study team will be unblinded. 6 months was chosen for unblinding as we know from prior studies that the median time for participants to reach maximum benefit from GAE is at least 3-months [10]. More importantly, we need a time period long enough to formally capture the placebo effect, whilst considering a time reasonable for participants to remain in the sham arm to maximise study recruitment, and minimise drop out.

GAE will be performed using 100-micron Embozene™ embolisation particles and following previously described methods for GAE [6]. The pathological embolisation target of the genicular arteries that supply the diseased portion of the knee is determined by patient symptoms and classical hyperaemic blush on angiography. All genicular arteries pertaining to the patients pain/synovitis demonstrated on preceeding contrast-enhanced MRI will be interrogated. Cone-beam CT (Allura FD20, Philips, Amsterdam) with contrast (6 ml of 100% contrast, 0.3 ml/s, 6 s delay) will be performed to confirm the hyperaemic target. A sports ice pack will be placed on the skin surface of the knee corresponding to the area to be embolised, minimising non-target embolisation to cutaneous branches by temporary vasoconstriction. The vessels will be embolised with 0.1–0.3 ml of embolic agent at a time to prune the abnormal vessels. The sham procedure will be identical to the GAE procedure, except that 2 ml heparinised 0.9% saline, instead of the embolic agent, will be slowly injected. Participants will be monitored for 4 h post-procedure.

Follow-up data will be collected at 1, 3, 6, 12, and 24 months post-randomisation (Table 2).

**Table 2 Tab2:** Participant timeline

Timepoint	Study period														
	Enrolment	Allocation and treatment		Post-allocation						Post-treatment crossover to GAE after unblinding					
		Pre-Tx	Tx	1 week	1 mos^a^	3 mos^a^	6 mos^b^	12 mos^b^	24 mos^b^	1 week	1 mos^a^	3 mos^a^	6 mos^b^	12 mos^b^	18 mos^b^
*Enrolment*															
Informed Consent	X														
Demographics, medical history	X														
*Interventions*															
Randomisation		X													
GAE			X												
Sham			X												
Crossover to GAE							X								
*Assessments*															
Eligibility confirmation	X														
KOOS, VAS	X				X	X	X	X	X		X	X	X	X	X
Analgesia questionnaire	X				X	X	X	X	X		X	X	X	X	X
EQ-5D-3L	X						X	X	X				X	X	X
Knee MRI		X					X	X					X	X	
Neuroscience assessments		X													
Pre-existing conditions		X													
PROM				X						X					
Opinion of intervention					X		X								
AE check					X	X	X	X	X	X	X	X	X	X	X
Study completion									X						X
Durability of GAE									X						X

^a^** ± **5 days

^b^** ± **10 days

At 6 months post-randomisation, after unblinding, sham participants will have the option to undergo the GAE procedure (crossover). Participants electing to cross over will have 18 months of post-GAE follow-up.

Subjects may use analgesia, as indicated, throughout the study. Analgesia use will be collected from a participant self-reported analgesia questionnaire.

#### Pain, Function, and Quality of Life Assessment

Knee Injury and Osteoarthritis Outcome Score (KOOS) is a validated questionnaire used within the orthopaedic literature to assess the effect of interventions on the perceived severity of knee OA [12] and has previously been reported in the GAE literature [5, 6]. KOOS is intended to be used over short- and long-term time intervals, to assess changes from week to week induced by treatment (medication, operation, physical therapy) or over years following a primary injury or OA. KOOS is responsive to change following non-surgical and surgical interventions (Online Appendix A). The primary outcome measure for the current study is improvement in the 4 Knee Injury and OA Outcome Score subscales (KOOS_4_), covering pain, symptoms, activities of daily living, and quality of life at 6 months in patients with mild to moderate knee OA. Sports and recreation were the most inconsistently reported measure from Genesis, hence its exclusion [6]. Total KOOS will be analysed as a secondary endpoint. The Minimum Clinically Important Difference (MCID) will be used to define clinical success. A 10-point increase in KOOS scores will be used to define the MCID based on the work by Roos [6, 12]. The proportion of participants achieving the MCID at 6 months will be compared between the GAE and sham treatment for all 5 KOOS subscales. In addition to the quality of life assessment from the KOOS questionnaire, the EuroQoL-5D (EQ-5D-3L) will be completed.

A visual analogue scale (0–100) will also be used to assess pain in the affected knee. This will be performed at baseline, with participants with a VAS < 50 excluded.

Analgesia use will not be controlled throughout the study. Participants will be asked if they are taking analgesia specific to their knee pain at follow-up, enabling longitudinal trends in analgesia use to be compared to treatment response following GAE or the sham procedures.

Pain, function, analgesia, and quality of life assessment data will be prospectively collected using a purposely designed Electronic Data Capture System (EDC).

#### Psychosocial Pain Assessment

Prior to the embolisation procedure, participants will attend a neuropsychological presurgical assessment. Previous research has demonstrated a role for central sensitisation in the maintenance and chronification of Osteoarthritis [11]. It is hypothesised that characterisation of the likely contribution of such processes on an individualised basis will help to better account for treatment response. Participants will undergo brain functional magnetic resonance imaging (fMRI), quantitative sensory testing, a short behavioural experiment and fill out questionnaires assessing personality and emotional reactivity. The study will examine measures previously shown to predict the development of chronic pain, including neural (e.g. resting state connectivity of amygdala and ventral striatum and levels of metabolites, such as GABA or glutamate, within pain modulatory regions) and behavioural (conditioned pain modulation, temporal summation) biomarkers [13]. To examine psychological mechanisms, participants will complete a well-established behavioural experiment called the Wisconsin Card Sorting Task (WCST). The WCST is a useful behavioural quantifier of psychological flexibility and may be a useful variable of interest when attempting to stratify patients that achieve optimal clinical outcomes from this surgical procedure. To measure personality and emotional or pain reactivity, the following will also be administered: Pain Catastrophizing Scale, Committed Action Questionnaire, the Patient Health Questionnaire, Intolerance of Uncertainty measure, the Generalised Anxiety Disorder Inventory, the Five Factor Mindfulness Short-form Questionnaire, Psychological Inflexibility in Pain Scale, Pain Interference measure, and the Pittsburgh Sleep Quality Index (Online Appendix As). These will be used to model individual differences in treatment response (as measured using the KOOS and VASs).

#### Knee MRI

Participants will have *T*2-weighted, *T*1-weighted, STIR (Short Tau Inversion Recovery), and contrast-enhanced MRI sequences of the affected knee. Whole-Organ Magnetic Resonance Imaging Score (WORMS) will be used to provide a semi-quantitative non-invasive assessment of synovial hypertrophy and neo-vascularisation of the treated knee at baseline, 6, and 12 months post-procedure [14]. Images will be assessed by two independent consultant radiologists with training in WORMS, who are blind to treatment arm. Inter-observer agreement will be calculated.

### Outcome Measures

The research staff collating follow-up data will be blind to treatment allocation (double blind).

### Primary Outcomes

*Efficacy* Change in mean score on 4 Knee Injury and OA Outcome Score subscales, covering pain, symptoms, activities of daily living, and quality of life (KOOS4) at 6 months post-randomisation.

### Secondary Outcomes with Hypothesis Testing

Clinical success: Proportion of subjects reporting ≥ 10-point improvement in KOOS scores, where a 10-point change from baseline is defined as the minimum clinically important difference (MCID) at 6 months post-randomisation.Pain relief: VAS change through 6 months post-randomisation.

### Secondary Outcomes with Descriptive Statistics

*OA symptom relief* Proportion of subjects reporting ≥ 10-point improvement in KOOS scores for each of the 5 KOOS subscales at 6 months post-randomisation*Safety* The proportion of subjects experiencing relevant adverse events that are possibly, probably, or definitely related to treatment received, GAE or Sham, from randomization through 6 months post randomization will be summarized by severity and compared between GAE and sham arms [15].*Synovial hypertrophy and neo-vascularisation* Whole-Organ Magnetic Resonance Imaging Score (WORMS) [14] at 6 months post-randomisation*Neural and behavioural indicators of predisposition to central facilitation of pain* Three assessments quantifying (1) sensory pain profiles, (2) psychological profiles, (3) individual differences in neurochemistry and functional connectivity, with psychological profile quantified and calibrated for pain sensitivity and modulatory ability at 6 months post-randomisation*Quality of life* Pre- and post-intervention EuroQoL-5D (EQ-5D-3L) for GAE versus non-crossover sham participants at 6 months post-randomisation*Patient-reported acceptability of study procedure* Questionnaire 1 week after GAE

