### Safety

The investigator will oversee study safety, including documenting and assessing all of participants’ AEs, regardless of severity or attribution. The number and type of serious AEs (SAEs) will be evaluated regularly, and procedure-related SAEs will also trigger assessment of whether any changes are needed to the protocol, patient informed consent, or other study documents or procedures.

After 5 subjects underwent GAE, GAE, and sham procedures stopped. A short safety and performance report was submitted to the MHRA for review. The MHRA made the determination that the study could resume based on this initial analysis.

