### Statistics

#### Endpoints

All efficacy analyses will be performed on the intention-to-treat population (all randomised subjects).

Change of KOOS4 (mean of pain, symptoms, activities of daily living, and quality of life subscores) will be compared between GAE and sham treatment arms in an ANCOVA model (vs. treatment arm indicator and baseline KOOS4 score). A secondary ANCOVA model will further include pain medication taken through 6 months.

The proportion of subjects achieving the MCID (10 points) will be compared between the sham treatment and GAE arms by Fisher’s exact test for all 5 KOOS subscales.

Subjects’ 6-month VAS will be compared between GAE and sham treatment arms in an ANCOVA model (vs. treatment arm and baseline pain score). Should the VAS be generally low, score will be dichotomised to with (> 0) or without pain (= 0), and a logistic regression analysis will be performed.

All 5 subscales of the KOOS questionnaire will be analysed at 6 months follow-up. Each sub-scale will be compared between the GAE and sham arms in an ANCOVA model (vs. treatment arm indicator and the baseline sub-scale score). An additional analysis will further include investigational site in the model.

All remaining endpoints will be descriptive, and formal hypothesis testing will not be performed. Continuous data will be reported as mean, standard deviations, median, minimum, and maximum. Categorical data will be summarised as frequency and proportions.

The proportions of subjects experiencing relevant adverse events that are possibly, probably, or definitely related to treatment received, GAE or sham treatment, from randomisation through 6 months post-randomisation will be summarised by severity and compared between GAE and sham arms.

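### Table 2 has an adverse event check at 1 week after crossover GAE but none at the existing 1-week contact in the sham-controlled phase, and the stated between-arm comparison covers only events judged related

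*Protocol article*

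**What the plan says.** **Outcome.** Protocol article, Secondary Outcomes with Descriptive Statistics: the safety outcome is the proportion of participants with "relevant adverse events that are possibly, probably, or definitely related to treatment received", counted "from randomization through 6 months post randomization". The Endpoints part of Statistics repeats the same restricted set, which "will be summarised by severity and compared between GAE and sham arms". Neither place states a comparison of all AEs by arm. The article does not define which events count as relevant, though the outcome sentence cites a reference.

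**Collection.** The Safety section has the investigator "documenting and assessing all of participants’ AEs, regardless of severity or attribution", and adds: "The number and type of serious AEs (SAEs) will be evaluated regularly". The GAE/Sham Procedure section says: "Participants will be monitored for 4 h post-procedure".

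**Schedule.** In Table 2, the AE check row is marked in the randomised phase at 1, 3, 6, 12 and 24 months. In the crossover phase it is marked at 1 week and at 1, 3, 6, 12 and 18 months. The PROM row, which is the acceptability questionnaire ("Questionnaire 1 week after GAE"), is marked at 1 week in both phases.

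**The concern.** The same procedure has a scheduled AE check at 1 week when it is given open-label after crossover. It has none when it is given under randomisation, which is the phase where a sham control allows events caused by embolisation to be told apart from those of catheterisation in general. The article gives no reason for the difference.

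Short-lived procedural events would be expected in the first days. If they are first asked about at 1 month (±5 days), mild ones that have resolved may be forgotten or never raised. The reported outcome is a proportion of participants, so it would be affected directly.

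A second point bears on the same result. The only between-arm comparison stated passes through two judgements, relevance and relatedness, although the unfiltered data are to be collected. A comparison of all events by arm depends on neither judgement.

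**Working it through.** **1. Is the Table 2 gap real or a fault of text extraction?** Each row's marks were matched to the column headers.

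| Row | Randomised phase | Crossover phase |
|---|---|---|
| AE check | 1, 3, 6, 12, 24 months | 1 week; 1, 3, 6, 12, 18 months |
| PROM | 1 week | 1 week |
| KOOS, VAS | enrolment; 1, 3, 6, 12, 24 months | 1, 3, 6, 12, 18 months |

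The PROM row falls exactly on the two 1-week columns and the KOOS row skips both, so the columns line up. The GAE/Sham Procedure section also lists post-randomisation follow-up from 1 month onward. The asymmetry is in the printed schedule.

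**2. What covers the interval from treatment to 1 month?** There are 4 hours of monitoring, then no scheduled AE check until 1 month. The duty to document all AEs and the regular review of serious AEs continue throughout, but no scheduled question prompts a report of a mild event.

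**3. Which quantities would a loss affect?** The article gives no AE rate, and its only computed figure, the KOOS4 sample size, has no bearing here. The following is therefore an illustration on assumed rates.

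Let P_G and P_S be the true proportions of participants with an event, and m the share of those participants whose events go unrecorded, taken as equal in both arms.

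- Observed proportions: P_G(1 − m) and P_S(1 − m)
- Observed risk difference: (1 − m)(P_G − P_S)
- Observed risk ratio: P_G(1 − m) / [P_S(1 − m)] = P_G / P_S

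| m | Difference, 20% v 10% | Ratio | Difference, 30% v 10% | Ratio |
|---|---|---|---|---|
| 0 | 10 points | 2.0 | 20 points | 3.0 |
| 10% | 9 points | 2.0 | 18 points | 3.0 |
| 25% | 7.5 points | 2.0 | 15 points | 3.0 |
| 50% | 5 points | 2.0 | 10 points | 3.0 |

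For example, 0.75 × (20 − 10) = 7.5. An equal loss shrinks the proportions and the absolute difference and leaves the ratio alone. Equal m is itself an assumption. The shared schedule and blind collation of follow-up data (Outcome Measures) support it but do not guarantee it.

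**4. What is collected against what is compared.** The Safety section collects all AEs regardless of attribution. The outcome and Endpoints text compare a subset. The restriction narrows the table, not the data, so a table of all AEs by arm needs no new data.

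**The case against.** The strongest reply is that nothing is shown to be lost. All AEs are to be documented, serious AEs are reviewed regularly, participants are observed for 4 hours, and the 1-month check can pick up earlier events in retrospect. The article also condenses a fuller protocol, which may set out AE procedures, and tables of all AEs are commonly left to an analysis plan. Much of this stands, and it rules out three stronger readings that a reader might infer.

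- **That the GAE-versus-sham safety result is shown to be under-ascertained.** Restricting the comparison to related events does not restrict collection. Both randomised arms follow one schedule, so the missing check does not by itself favour either. Under-recording of mild early events is a risk, not a demonstrated loss.
- **That attribution is biased by knowledge of the arm.** The article says "an unblinded trained radiographer will inform the staff performing the study procedure" of the allocation, but nowhere says that those staff judge relatedness. Assessment is given to the investigator, and unblinding of the study team is set at 6 months, which implies that the team is blind until then. Whether the assessing investigator also performs procedures is not stated.
- **That crossover GAE will look twice as harmful as randomised GAE.** No such AE comparison is planned. The figure also rests on assumptions: a 20% event rate in week 1, complete capture at a 1-week check, and 30% to 50% not recalled at 1 month. These give 20 × 0.7 = 14% and 20 × 0.5 = 10%, hence ratios of 20/14 = 1.43 and 20/10 = 2.0. Doubling is only the upper end.

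What the reply does not remove is a printed schedule whose two halves disagree, with the sparser half in the controlled phase.

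**Conclusion.** The point holds as an inconsistency in the schedule with a modest, avoidable risk to safety reporting. As printed, early short-lived events in the sham-controlled phase depend on recall at 1 month or on spontaneous report, while the same events after crossover GAE are asked about at 1 week. The likely direction is lower reported proportions in both arms and a smaller absolute difference between them. The size cannot be derived from the article, and the table above shows only how an assumed equal loss would act.

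The related-only comparison is a separate and lesser matter. It is a choice of what to report, and it leaves the stated safety comparison resting on attribution judgement when data free of that judgement will be in hand.

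The conclusion assumes that Table 2 shows the schedule actually in use. If AEs are already asked about at 1 week in the randomised phase, only the table needs correcting.

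**What to change.** 1. Reconcile the AE check row of Table 2 by adding a mark at the existing 1-week contact of the randomised phase. Ask the same question, in the same words, in both arms. The outcome text ties the 1-week questionnaire to GAE, while Table 2 does not separate the arms. A question put to GAE participants alone would create the very imbalance that is now absent.
2. Report all AEs and all serious AEs by arm through 6 months, as numbers and proportions of participants, beside the planned comparison of relevant treatment-related events.
3. Some participants have already been treated (the Safety section describes a review after five GAE procedures), so record the contact at which each event was first reported. Events found through the added check can then be identified.

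The cost is one question at a contact that already takes place, one further table, and a few more minor AEs reported. The definitions of the primary and secondary outcomes do not change.

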### Exploratory Outcomes

*Analgesia intake reduction from baseline* Analgesia questionnaire through 6 months post-randomisation*Durability* Time from GAE procedure to next invasive intervention for knee OA*Comparative cost-effectiveness* Payer-perspective health economic analysis of GAE versus standard of care, including integration of EQ-5D-3L-based quality-adjusted life-years, and durability.*GAE group outcomes* KOOS, EQ-5D-3L, analgesia questionnaire, and VAS at 1, 3, 6, 12, and 24 months post-randomisation*PROMs for sham treatment without crossover versus GAE* 12 and 24 months post-randomisation*Imaging changes GAE versus sham* WORMS at 12 and 24 months post-randomisation*Sham group outcomes* KOOS, VAS, and analgesia questionnaire diary at 1, 3, 6, 12 (crossover), and 18 months (crossover); EQ-5D-3L at 6, 12 (crossover), and 18 months (crossover); MRI at 6 and 12 months (crossover) post-randomisation.

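### Read literally, the 6-month EQ-5D-3L comparison drops sham participants who later choose crossover, although none has had GAE in the trial by then

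*Protocol article*

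**What the plan says.** Under Secondary Outcomes with Descriptive Statistics, the quality-of-life outcome is EQ-5D-3L before and after intervention, "for GAE versus non-crossover sham participants at 6 months post-randomisation".

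The timing of crossover is given under GAE/Sham Procedure:

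- Unblinding: "At 6 months post-randomisation, the participants and the study team will be unblinded".
- The offer: "At 6 months post-randomisation, after unblinding, sham participants will have the option to undergo the GAE procedure (crossover").
- Its elective nature: "Participants electing to cross over will have 18 months of post-GAE follow-up".

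Table 2 puts the 6-month EQ-5D-3L and the crossover in the same column.

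The Endpoints section under Statistics sets the general population: "All efficacy analyses will be performed on the intention-to-treat population (all randomised subjects"). It also fixes the status of outcomes such as this one: "All remaining endpoints will be descriptive, and formal hypothesis testing will not be performed".

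Under Exploratory Outcomes, a similar restriction appears for 12 and 24 months: "PROMs for sham treatment without crossover versus GAE".

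**The concern.** Restricting the control arm to those who did not cross over is normally meant to keep out control participants who have already received the active treatment. At 6 months there are none to keep out, because the offer comes only then and only after unblinding. The restriction can therefore do one thing only: remove sham participants according to a decision taken at or after the time the outcome is measured, with the allocation known. The GAE arm has no matching filter.

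What is at stake is the reported quality-of-life contrast. As randomised, it is a clean sham-controlled comparison. With the restriction it compares a whole arm with a self-selected part of the other. It would also rest on a different sham group from the other 6-month outcomes (KOOS4, the responder proportions, VAS, WORMS), none of which carries the restriction.

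**Working it through.** **1. Order of events at 6 months.**

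| Element | What the article fixes | Where |
|---|---|---|
| Outcome time | 6 months post-randomisation | Secondary Outcomes with Descriptive Statistics |
| Unblinding | 6 months | GAE/Sham Procedure |
| Crossover | Optional, at 6 months, after unblinding | GAE/Sham Procedure, Table 2 |
| Sham group compared | Non-crossover only | Secondary Outcomes with Descriptive Statistics |
| General rule | All randomised subjects | Statistics, Endpoints |

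Crossover status is settled no earlier than the outcome. Selecting on it departs from the randomised comparison whatever drives the choice, and it does not fit the general rule in the last row.

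**2. The article's own figures (Sample Size).** With a difference of 6.4, SD 10, two-sided alpha 0.05 and power 0.85:

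n per arm = 2 × (1.960 + 1.036)² × 10² / 6.4² = 43.8, rounded up to 44, so 88 in total. Then 88 / (1 − 0.20) = 110.

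Both stated figures reproduce and are not in dispute. They give the starting point used below: 44 evaluable participants per arm.

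**3. Possible size of the selection effect.** The article gives no crossover share and no determinants of the choice, so both inputs here are assumptions:

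- c: share of sham participants who cross over, 30%, 50% or 70%.
- ρ: correlation between a latent tendency to decline crossover and the participant's own 6-month score, 0, 0.3 or 0.5. A positive ρ means that those who feel better decline more often.

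With standardised scores and no true treatment effect, the mean of the retained sham group is shifted by

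ρ × φ(z_c) / (1 − c),

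where z_c is the c-quantile of the standard normal. GAE minus sham is shifted by the negative of this. The multiplier φ(z_c)/(1 − c) is:

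- c = 30%: 0.348 / 0.70 = 0.50
- c = 50%: 0.399 / 0.50 = 0.80
- c = 70%: 0.348 / 0.30 = 1.16

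The standard-error ratio is √(1/44 + 1/m) / √(2/44), with m the number of sham participants kept out of 44.

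| Crossover c | Sham kept, m | Shift, ρ = 0 | Shift, ρ = 0.3 | Shift, ρ = 0.5 | SE ratio |
|---|---|---|---|---|---|
| 30% | 31 | 0 | −0.15 SD | −0.25 SD | 1.10 |
| 50% | 22 | 0 | −0.24 SD | −0.40 SD | 1.22 |
| 70% | 13 | 0 | −0.35 SD | −0.58 SD | 1.48 |

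A simulation of 2,000,000 standardised scores gives the same shifts to two decimals, apart from noise of at most 0.002 SD at ρ = 0.

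**4. After the fix.** With every randomised sham participant kept, the comparison is 44 v 44 after the planned dropout (about 55 v 55 randomised), and this source of bias is zero.

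**The case against.** **The phrase may mean the sham arm before crossover.** Table 2 has two 6-month EQ-5D-3L columns, one counted from allocation and one within the block that follows crossover. Under Exploratory Outcomes, the sham-group item uses crossover as a tag for that later series. On this reading every sham participant counts as non-crossover at 6 months post-randomisation, nobody is dropped, and the all-randomised rule is respected. This is possible. It is not what the words say: they describe participants, not a visit. The 12- and 24-month item uses near-identical wording for a real subgroup, and no other 6-month outcome is qualified in this way. Even on the kinder reading, the phrase needs clarifying.

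**The outcome is descriptive.** This is correct, and it limits the weight of the point. It does not remove it, since a between-arm summary from a sham-controlled trial will be read as an effect of treatment whether or not a test is attached.

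**The direction of bias is conjecture.** This stands in part. A reader might infer that the choice is driven by the 6-month result, but the article says only that crossover is optional. Declining could also reflect poor health or reluctance to have a second invasive procedure. The loss of the randomised comparison does not depend on the driver. The sign and size of any bias do.

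**The 12- and 24-month comparison is exploratory and its label names the subset.** This stands. Comparing by randomised group at those times would answer a different question, so it is not a correction that the article needs. A label saying that the contrast is non-randomised is enough.

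**Conclusion.** The point holds as a fault in how one descriptive secondary outcome is defined. As worded, the 6-month EQ-5D-3L comparison filters the sham arm alone on an elective choice made at or after the outcome, removes no contamination, and conflicts with the all-randomised rule.

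If sham participants who feel worse cross over more often, the contrast is biased against GAE by about 0.15–0.58 SD, with a standard error 10–48% larger. Those figures rest on assumed crossover of 30–70% and an assumed correlation of 0.3–0.5. With no correlation the bias is zero, though the loss of precision remains.

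Two wider inferences are not supported. The first is that the main efficacy result is compromised: KOOS4, its power, the tested responder proportion and VAS carry no crossover restriction. The second is that the economic analysis inherits the problem. It is described as "including integration of EQ-5D-3L-based quality-adjusted life-years, and durability", but the article does not say that its sham data are limited to non-crossover participants, so an effect on the QALYs is not shown.

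**What to change.** Under Secondary Outcomes with Descriptive Statistics, reword the quality-of-life item along these lines: *EQ-5D-3L at baseline and 6 months, GAE versus sham, all randomised participants.* If the sham arm before crossover was what was meant, the same wording settles it.

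Keep any non-crossover subset, including the exploratory 12- and 24-month PROM comparison, as a separate summary labelled non-randomised.

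The cost is wording only. Table 2 already schedules EQ-5D-3L at enrolment and at 6 months, so no participants, visits or data are added. The change should be made before unblinded data are analysed.
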